***Study implementation***

***Anesthesia and monitoring methods***

All patients will be fasting for 6-8 h and water deprivation for 2 h before operation, and will not receive any preoperative medication. Baseline blood pressure and heart rate will be obtained in the preoperative preparation area. After entering the operating room, patients will receive a standard monitoring including electrocardiography (ECG) and pulse oximetry (SpO2). An intra-arterial cannula will be placed in the radial artery for continuous arterial pressure measurement. Anesthetic depth will be measured using the Bispectral index. End-tidal carbon dioxide concentration (PetCO2) will be monitored after intubation. The participants will be divided into the total intravenous anesthesia group (group T) or the inhalation anesthesia group (group C) according to the allocation.

***Intravenous anesthesia induction***

All patients will be continuously infused with 0.9% sodium chloride at the rate of 6-8 mL/kg/h, and preoxygenated with 100% oxygen at the rate of 6 L/min through the mask during the induction period .The two groups will receive the same anesthesia induction methods : 1.5–2mg/kg of propofol, if the BIS value is ≤ 60, 2 mg/kg of cisatracurium and 0.5μg/kg of sufentanil will be administered. If the BIS value is *>* 60, 1 mg/kg of propofol will be immediately added, with an interval of *>* 1min between each bolus, until the BIS value is ≤ 60. Volume-controlled ventilation will be performed (tidal volume 6–8 ml/kg, respiratory rate12–18 times/min and PEEP 5 cmH₂O ) after endotracheal intubation.

***Anesthesia maintenance***

Anesthesia maintenance is defined as the time from the end of induction to the cessation of anesthesia (the infusion or inhalation of anesthetic drugs will be stopped immediately after the end of surgery). Group T will receive continuous propofol infusion at a rate of 4–12 mg/kg/h for maintenance, whereas Group C will receive inhalation of sevoflurane at 1.0-3.0% for maintenance. Remifentanil will be administered at a rate of 0.05–0.2 μg/kg/min, cisatracurium and sufentanil will be added in both groups according to requirements of the surgery. The depth of anesthesia will be titrated to BIS values of 40–55 via the manual adjustment of propofol infusion or inhalation of sevoflurane. Upon completion of the surgery, all anesthetic agents will be discontinued. All patients will be provided with patient-controlled intravenous analgesia (PCIA) (1.5 μg/kg of sufentanil + 0.9% normal saline, total volume 100 ml 2 ml/h for 48 h). The self-controlled capacity and the locking time will be 0.5ml and 15 minutes, respectively.

***Recovery of anesthesia***

After tracheal extubation, patients will be transferred to a post-anesthesia care unit (PACU) and receive oxygen supplementation of 3 L/min via a nasal catheter. When the Steward awakening score ≥4 points is reached, patients will be discharged from the PACU to the surgical wards.

***Outcomes***

***Primary outcomes***

The primary outcome of this study is global Quality of Recovery-40 (QoR-40) score on POD 1. The QoR-40 contains 40 items assessing five dimensions of recovery: emotions, physical comfort, psychological support, physical independence, and pain, which scores range from 40 to 200. QoR-40 has been widely used in clinical practice and research for various surgical types and anesthesia techniques.

***Secondary outcomes***

The secondary outcomes include QoR-40 score on POD 2 and POD 3, levels of proinflammatory cytokines (tumor necrosis factor-α, interleukin -1β, and interleukin -6), hemodynamic parameters, arterial and end tidal carbon dioxide pressure, pain scores at rest and while coughing, extubation time , length of PACU stay, ramsay sedation score on awakening, awakening time , adverse events (postoperative nausea and vomiting, headache, respiratory depression ,hypoxemia).

***Sample size estimation***

The primary outcome that will be assessed in this study is the QoR-40 score on postoperative day (POD) 1. Previous studies reported that the minimal clinically important difference (MCID) of QoR-40 score was 6.3 points[10], based on our institutional data, the Standard Deviation was 9.3 points. Based on this assumption, 36 patients in each group would be required with a power of 80% and at an α level of 0.05. To allow for 10% possible dropouts, a total of 80 patients (n = 40 in each group) will be enrolled. The sample size is calculated using the PASS software (version 15.0.5, NCSS, LCC, Kaysville, UT).

***Data collection and registration***

Trained independent investigators who are unaware of group assignment will collect patients’ demographic data and baseline characteristics. The primary and secondary outcome measures as well as other non-outcome perioperative data will be collected. The values of MAP、HR、BIS、ETCO2 and PaCO2 will be recorded at five timepoints: baseline, 30 mins into the surgery, 60 mins into the surgery, the end of surgery, and immediately after tracheal extubation. Postoperative pain will be evaluated using the Numerical Rating Scale, ranging from 0 to 10 (0=no pain, 10=the most severe imaginable pain). Levels of proinflammatory cytokines and NRS will be recorded at postoperative 2,6,24h. All data will be entered into the electronic case report forms(eCRFs) under the supervision of trained research personnel. Investigators will conduct an interim analysis to make an informed decision on whether to continue the trial or modify the study design to optimize the trial results. After the completion of data registration, the electronic database will be locked. After de-identification, the database will be sent to an independent statistician for statistical analysis.

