**Materials and methods**

This is a prospective, parallel, double-blinded, randomized controlled trial, which will be administered at the Guanyun People’s Hospital.

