***Statistical analysis***

The demographic data and baseline characteristics will only be expressed using descriptive statistics and will not be compared between groups. According to the data distribution, continuous data will be expressed as means and standard deviations, or median and interquartile ranges. Categorical data will be presented as numbers and percentages. The differences between groups will be analyzed by independent t-test, repeated measures analysis of variance, or Mann Whitney rank sum test, Chi-squared test, or Fisher exact test as appropriate. All data will be analyzed using the SPSS software (version 21.0; IBM SPSS, Chicago, IL) by the independent statistician. A two-sided P value < 0.05 indicates a statistically significant difference.

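### The investigator-run interim analysis, with open-ended freedom to redesign, leaves the stated 5% error rate and the double blinding unprotected

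*Protocol*

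**What the plan says.** The interim analysis appears in one sentence of the Protocol, Data collection and registration: "Investigators will conduct an interim analysis to make an informed decision on whether to continue the trial or modify the study design". The sentence goes on to give the aim of a redesign, and the full clause reads "modify the study design to optimize the trial results". It therefore fixes who acts (the investigators), what they may do (continue, or change the design) and why. It does not bound the changes.

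Other sections bear on it:

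- Sample size estimation plans a single test: "36 patients in each group would be required with a power of 80% and at an α level of 0.05", raised to 40 per group for 10% dropout.
- Statistical analysis states "A two-sided P value < 0.05 indicates a statistically significant difference", with no reference to an interim look. It gives the analysis of all data to the independent statistician.
- Data collection and registration sends the de-identified database to that statistician only after lock.
- Materials and methods calls the study a "prospective, parallel, double-blinded, randomized controlled trial". Withdrawal criteria lists knowledge of the grouping by subjects or researchers, above 20%, as a ground for withdrawal.

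**The concern.** A nominal 5% error rate holds for one test of a design fixed in advance. It need not hold if the people running the trial can compare the groups part-way and then stop, or alter the remaining design in the light of that comparison. A final P just below 0.05 could not then be taken at face value, and the estimated difference could be pulled towards the interim trend.

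Blinding is also at stake. The primary outcome is a patient questionnaire collected by study staff, so knowledge of interim results by group among the investigators could affect how the rest of the trial is run and assessed.

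The protocol also contradicts itself on who analyses the data and when. An investigator-run look before lock does not fit with analysis of all data by an independent statistician who receives the database after lock.

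**Working it through.** **Inputs from the protocol (Sample size estimation, Statistical analysis).** "minimal clinically important difference (MCID) of QoR-40 score was 6.3 points"; "the Standard Deviation was 9.3 points"; 80% power; two-sided alpha 0.05; 36 per group; 10% dropout; 80 in total, 1:1.

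**Inputs that are assumptions.** The protocol gives no timing, number of looks or decision rule. The base case is one look at half information. The range is 25% to 75% information, and one to three equally spaced interim looks.

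**Step 1: the plan's own figure.** The normal approximation gives n = 2(1.960 + 0.842)² × 9.3² / 6.3² = 34.2, so 35 per group. The exact t-test calculation gives power of 79.8% at 35 and 80.9% at 36, so 36 per group. Then 36 / 0.90 = 40 per group, 80 in total. The stated figures reproduce, for a design with a single test.

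**Step 2: an efficacy look at 0.05, then a final test at 0.05.** With Z₁ the interim and Z₂ the final statistic, correlated √t at information fraction t, the type I error is 1 − P(|Z₁| < 1.96 and |Z₂| < 1.96).

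| Looks before the final test | Two-sided type I error |
| --- | --- |
| One, t = 0.25 | 9.1% |
| One, t = 0.50 | 8.3% |
| One, t = 0.75 | 7.3% |
| Two, equally spaced | 10.7% |
| Three, equally spaced | 12.6% |

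**Step 3: no efficacy stop, but the second-stage size is chosen from unblinded half-way results.** Count sample size in units of the planned total, so that stage one is 0.5 and stage two is m. The unadjusted final statistic is (√0.5·Z₁ + √m·Z)/√(0.5 + m), where Z is the independent stage-two statistic. Given Z₁ = z, the chance of a false rejection is

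A(z, m) = 1 − Φ[(1.96√(0.5 + m) − √0.5·z)/√m] + Φ[(−1.96√(0.5 + m) − √0.5·z)/√m].

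The worst case takes the m that maximises A at each z and averages over the standard normal distribution of Z₁.

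| Permitted m | Meaning | Worst-case two-sided error |
| --- | --- | --- |
| 0.5 only | No change (check) | 5.0% |
| 0.5 to 1.5 | Total between planned and twice planned | 6.2% |
| Near 0 to 1.5 | Stage two may also be cut | 9.9% |
| Near 0, no upper limit | Unrestricted | 11.2% |

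**Step 4: what a controlled look would cost.** At half information, O'Brien-Fleming bounds of P < 0.0052 and then P < 0.0480 hold the overall error at 5%. Haybittle-Peto (P < 0.001, then 0.05) gives 5.02%. By normal approximation, power at 36 per group is 81.7% with O'Brien-Fleming against 82.0% for the fixed design.

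**The case against.** The strongest reply is that the protocol nowhere says the look is unblinded, compares the groups or can stop for efficacy. The section opens with data collectors who do not know the allocation. Deciding whether to continue could mean futility or safety, and Ethical considerations and declarations provides for continuous safety assessment. The independent statistician could prepare a blinded summary for the investigators. A blinded look, or one that can stop only for futility, does not inflate the type I error. This stands. A reader might infer that the 5% error rate and the blinding are already lost, but the text does not support that. It permits such a look without stating it.

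Second, timing, boundary and alpha spending are commonly left to a statistical analysis plan, which may exist but is not shown, and the 0.05 threshold may be only a general convention. This also stands: the lack of a boundary is not the finding. But a statistical analysis plan that added one would still have to override what the protocol itself states, namely investigators running the look, an unbounded right to redesign, and optimising results as the aim.

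Third, the size of the inflation is easy to overstate. A reader might take the closed-form one-sided bound for an unrestricted sample size change, 0.025 + exp(−1.96²/2)/4 = 0.025 + 0.0366 = 0.0616, and double it to about 12%. That doubling is not valid, because one adaptation rule cannot be the worst case for both tails at once. The direct two-sided maximum is 11.2%, and it needs complete freedom over the second-stage size, which is remote for an 80-patient trial at one hospital. A change of endpoint or population is not excluded by the text, but the protocol names neither and neither is quantified here.

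**Conclusion.** The point holds as a failure of protection. The protocol gives investigators an interim look with unlimited scope to redesign for better results, keeps a single-test 0.05, and contradicts its own assignment of the analysis. Every inflation figure above is conditional on a between-group comparison leading to an efficacy stop or a results-driven change of sample size, and on the assumed timing and number of looks. For a single look, those figures run from 6.2% to 11.2% in place of 5%. Confidence is high on the wording and the internal conflict, and moderate on blinding, where the harm is permitted but not stated. The clause should be amended before any look takes place, because a redesign made after seeing results by group cannot be undone in the analysis.

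**What to change.** In Data collection and registration, delete the option to "modify the study design to optimize the trial results". Restrict any look by investigators to safety data without group comparison and the blinded pooled SD of the POD 1 QoR-40 score, set against the planned 9.3. When reading that SD, allow for the fact that ignoring group adds any true difference: with 1:1 allocation and a difference of 6.3, the expected value is √(9.3² + 6.3²/4) = √96.4 = 9.8.

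If a comparative look is wanted, state that the independent statistician does it once, at a prespecified time and under a valid boundary. Haybittle-Peto or O'Brien-Fleming, as in step 4, would both serve. Investigators stay blind, and no other results-driven design change is allowed. Align the sentences on the statistician's role and on database lock, and make the final significance level in Statistical analysis match the boundary chosen.

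The cost is a short amendment of a few sentences and no extra patients. What is given up is the freedom to redesign mid-trial.

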***Statistical analysis***

The demographic data and baseline characteristics will only be expressed using descriptive statistics and will not be compared between groups. According to the data distribution, continuous data will be expressed as means and standard deviations, or median and interquartile ranges. Categorical data will be presented as numbers and percentages. The differences between groups will be analyzed by independent t-test, repeated measures analysis of variance, or Mann Whitney rank sum test, Chi-squared test, or Fisher exact test as appropriate. All data will be analyzed using the SPSS software (version 21.0; IBM SPSS, Chicago, IL) by the independent statistician. A two-sided P value < 0.05 indicates a statistically significant difference.

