**Introduction**

Compared with transperitoneal laparoscopic approach, retroperitoneoscopic approach has many advantages in urological surgery, such as shorter puncture path, shorter operative time, less blood loss, less postoperative pain, and faster recovery[1-4]. However, restricted to the retroperitoneal anatomy, the limited working space can make the procedure technically challenging, higher insufflation pressures (20–25 mmHg) of CO_2_ is needed to create a larger working space[5, 6]. More CO_2_ is absorbed into the blood, causing harm to the human internal environment.

Propofol-based total intravenous anesthesia (TIVA) and sevoflurane inhalation anesthesia are two general anesthesia techniques commonly used in clinical practice. Compared with inhalation anesthesia, whether TIVA can provide better postoperative quality of recovery is influenced by the type of surgery[7-9]. The Global Quality of Recovery- 40 (QoR-40) questionnaire was specifically designed to measure the health status of patients after surgery and anesthesia, and it involves 5 dimensions: physical comfort, physical independence, emotional state, psychological support and pain[10]. On the strength of its reliability and validity, QoR-40 has a broad clinical application[11, 12] . Peripheral inflammatory factors can lead to inflammatory reactions such as vasodilation, increased permeability, leukocyte exudation, and even increase the permeability of the blood-brain barrier. Inflammatory factors enter the central nervous system, neurons are damaged or die, resulting in brain tissue damage. By measuring and comparing the levels of perioperative inflammatory factors, we can predict the postoperative recovery of patients[13, 14].

Therefore, the objective of our study is to compare the effects of TIVA and inhalation anesthesia on the quality of recovery by using the QoR-40 questionnaire, and the levels of inflammatory factors in patients undergoing urological retroperitoneoscopic surgery.

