**Appendix A**

| Table 1 Schedule of patient enrolment, study interventions and outcome assessment | | | | | | | | | |
| --- | --- | --- | --- | --- | --- | --- | --- | --- | --- |
|  | Study period |  |  |  |  |  |  |  |  |
|  | Enrolment | Allocation | Post-allocation |  |  |  |  |  |  |
|  |  | 2 hours |  |  |  |  |  |  |  |
|  | Preoperative | before |  |  | POS | POS | POS | POS | POS |
| Time point | visit | surgery | intraoperatively | PACU | 2h | 6h | 24h | 48h | 72h |
| Patient enrolment |  |  |  |  |  |  |  |  |  |
| Eligibility criteria | **×** |  |  |  |  |  |  |  |  |
| Written informed  consent | **×** |  |  |  |  |  |  |  |  |
| Demographic data | **×** |  |  |  |  |  |  |  |  |
| Baseline  characteristics | **×** |  |  |  |  |  |  |  |  |
| Randomisation/ |  | **×** |  |  |  |  |  |  |  |
| allocation |  |  |  |  |  |  |  |  |  |
| Study interventions |  |  |  |  |  |  |  |  |  |
| Total intravenous |  |  | **×** |  |  |  |  |  |  |
| anaesthesia |  |  |  |  |  |  |  |  |  |
| Inhalation |  |  | **×** |  |  |  |  |  |  |
| anesthesia |  |  |  |  |  |  |  |  |  |
| Outcome assessment |  |  |  |  |  |  |  |  |  |
| QoR-40 scores | **×** |  |  |  |  |  | **×** | **×** | **×** |
| Postoperative pain  scores |  |  |  |  | **×** | **×** | **×** |  |  |
| Length of PACU  stay |  |  |  | **×** |  |  |  |  |  |
| Levels of | **×** |  |  |  | **×** | **×** | **×** |  |  |
| proinflammatory |  |  |  |  |  |  |  |  |  |
| cytokines |  |  |  |  |  |  |  |  |  |
| Hemodynamic |  |  | **×** |  |  |  |  |  |  |
| parameters |  |  |  |  |  |  |  |  |  |
| ETCO2 |  |  | **×** |  |  |  |  |  |  |
| PaCO2 |  |  | **×** |  |  |  |  |  |  |
| Awakening time |  |  | **×** |  |  |  |  |  |  |
| Extubation time |  |  | **×** |  |  |  |  |  |  |
| Level of sedation |  |  | **×** |  |  |  |  |  |  |
| PONV |  |  |  |  |  |  | **×** |  |  |
| Headache |  |  |  |  |  |  | **×** |  |  |
| Hypoxemia |  |  |  |  |  |  | **×** |  |  |
| Respiratory depression |  |  |  |  |  |  | **×** |  |  |
| According to SPIRIT statement of defining standard protocol items for clinical trials. | | | | | | | | | |
| QoR-40, 40 items of Quality of Recovery;PACU, post-anaesthesia care unit;  PONV, postoperative nausea and vomiting; POS, postoperative; | | | | | | | | | |
| ETCO2,end-tidal carbon dioxide;PaCO2,partial pressure of arterial carbon dioxide. | | | | | | |  |  |  |
| SPIRIT, Standard Protocol Items: Recommendations for Interventional Trials. | | | | | | | | | |

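### The serial secondary outcomes have pre-treatment values, but the Statistical analysis section names only unadjusted tests and does not say how baseline enters

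*Protocol*

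**What the plan says.** The Statistical analysis section of the protocol gives one list for all outcomes: "The differences between groups will be analyzed by independent t-test, repeated measures analysis of variance, or Mann Whitney rank sum test", then the chi-squared and Fisher tests, with the choice among them left to suitability. It ties no test to an outcome. It does not say which times enter a repeated measures ANOVA, or whether the group main effect or the group-by-time interaction is the test of interest. On baseline data it says only this: "The demographic data and baseline characteristics will only be expressed using descriptive statistics and will not be compared between groups".

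Pre-treatment values are collected nonetheless:

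- **MAP and HR.** Data collection and registration counts baseline among five times: "baseline, 30 mins into the surgery, 60 mins into the surgery, the end of surgery, and immediately after tracheal extubation". Anesthesia and monitoring methods places it before anaesthesia: "Baseline blood pressure and heart rate will be obtained in the preoperative preparation area".
- **PaCO2.** It shares the five times, but no section says when its baseline is drawn, and Table 1 marks PaCO2 only intraoperatively.
- **Cytokines.** Table 1 ("Schedule of patient enrolment, study interventions and outcome assessment") marks the preoperative visit and 2, 6 and 24 h. The text gives only the later three: "Levels of proinflammatory cytokines and NRS will be recorded at postoperative 2,6,24h".

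The Introduction includes in the objective "the levels of inflammatory factors in patients undergoing urological retroperitoneoscopic surgery". The Secondary outcomes section ranks the cytokines as secondary.

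**The concern.** Repeated measures ANOVA is the only longitudinal method listed, and for MAP and HR the protocol already counts baseline as one of the five times. Entering baseline as a level of the time factor is therefore an easy default. Randomisation makes the expected group difference at that level zero, so a group main effect that averages over it is pulled toward no difference by a fixed fraction. Testing the interaction instead avoids that averaging, but spreads a sustained effect over 3 degrees of freedom (cytokines) or 4 (MAP, HR). Dropping baseline leaves the estimate unbiased but forgoes whatever precision the pre-treatment value could give.

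At stake is a false report of no difference in inflammation, one of the two comparisons in the objective. The trial is sized on QoR-40 alone, so nothing in the protocol secures power for the cytokines.

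**Working it through.** **The plan's own figure.** The only sample size stated is for POD 1 QoR-40: difference 6.3, SD 9.3, two-sided 0.05, power 80%. The noncentral t gives 79.8% power at 35 per group and 80.9% at 36, so 36 is reproduced. 36/0.9 = 40 per group, 80 in total. No figure is given for any serial outcome.

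**Assumptions for the comparison (not in the protocol).** n = 36 per group, SD 1 at each time, no group difference at baseline, a constant difference d = 0.5 at each of m later times, and equal correlation r between all times. m = 3 for cytokines (by Table 1) and m = 4 for MAP and HR.

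**Formulas.** A patient-level summary with variance V gives a standard error of √(2V/n) for the group difference.

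- Main effect, baseline as a level: effect d·m/(m+1); V = (1 + m·r)/(m+1).
- Post-baseline times only: effect d; V = (1 + (m−1)r)/m.
- Post-baseline times with baseline covariate: effect d; V = (1 + (m−1)r)/m − r².
- Interaction: noncentral F with m and 70m df; noncentrality (n/2)·Σ(difference at each time − mean difference)²/(1 − r).

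Power for the first three comes from the noncentral t with 70 df (69 with the covariate).

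**Shrinkage.** With baseline as a level the main effect is 3/4 × 0.5 = 0.375 for cytokines and 4/5 × 0.5 = 0.40 for MAP and HR. The factors do not depend on r. In the two post-baseline analyses the factor is 1.

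**Cytokines at r = 0.5.**

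- Baseline as a level: V = 2.5/4 = 0.625, SE = 0.186, 0.375/0.186 = 2.01, power 51%.
- Post-baseline only: V = 2/3 = 0.667, SE = 0.192, 0.5/0.192 = 2.60, power 73%.
- Adjusted: V = 0.667 − 0.25 = 0.417, SE = 0.152, 0.5/0.152 = 3.29, power 90%.
- Interaction: the deviations from 0.375 are −0.375 and three of 0.125, with sum of squares 0.1875; 18 × 0.1875/0.5 = 6.75 on 3 and 210 df, power 56%.

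**Cytokines over the range of r.**

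| Analysis | r = 0.3 | r = 0.5 | r = 0.7 |
|---|---|---|---|
| Main effect, baseline as a level | 62% | 51% | 43% |
| Group-by-time interaction | 42% | 56% | 81% |
| Post-baseline only, unadjusted | 82% | 73% | 65% |
| Post-baseline, baseline as covariate | 88% | 90% | 96% |

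For one baseline and four later times at r = 0.5, the main effect with baseline as a level has 58% power against 93% adjusted.

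**Relaxing equal correlation.** A preoperative sample may predict postoperative values less well than these predict each other. Take pre-post 0.2 and post-post 0.5, cytokines:

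- Baseline as a level: V = (4 + 2(3×0.2 + 3×0.5))/16 = 0.5125, power 59%.
- Post-baseline only: V = 0.667, power 73%.
- Adjusted: V = 0.667 − 0.04 = 0.627, power 75%.

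With pre-post 0.3 and post-post 0.5, adjusted power is 79% against 73% unadjusted.

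**Relaxing the constant effect.** With differences of 0.75, 0.50 and 0.25 at 2, 6 and 24 h (same mean) and r = 0.5, the sum of squares is 0.3125, the noncentrality is 18 × 0.3125/0.5 = 11.25, and interaction power rises from 56% to 81%.

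**The case against.** The strongest reply is that there is no planned model to criticise. The list is generic; a t-test or Mann-Whitney test at each time is as much on it as repeated measures ANOVA and involves no averaging with baseline. Covariates, time levels and contrasts are commonly left to a statistical analysis plan, which is not shown. This stands against one tempting inference, that the planned cytokine comparison is biased toward no difference. That needs three things together: repeated measures ANOVA, baseline as a level of time, and the group main effect as the reported result. The protocol commits to none of them for any outcome.

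Two further inferences also fail. The text under Data collection and registration gives no preoperative cytokine sample; on that text alone a cytokine ANOVA has no baseline level. And the sentence restricting baseline data to description rules out between-group testing of baseline; it does not forbid a baseline covariate.

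The power gain is also not assured. Equal correlation favours adjustment, and a constant effect disfavours the interaction; relaxing either narrows the gaps, as shown above.

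What the reply does not remove is that the section names its methods, and no baseline-adjusted method is among them although the values are collected. Choosing the suitable test from that list cannot produce one.

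**Conclusion.** The point holds as a low-cost improvement to secondary analyses, not as a demonstrated bias. The shrinkage to 3/4 or 4/5 is exact, but only for a group main effect with baseline as a level. Otherwise the loss is one of power or precision. In the scenarios where all were computed, the adjusted analysis was more powerful than post-baseline values alone and than baseline as a level. Its advantage over post-baseline values alone ran from 2 percentage points (75% against 73%, weak pre-post correlation) to 31 (96% against 65%, equal correlation 0.7). All power figures rest on an assumed effect and assumed correlations, since the protocol supplies neither.

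MAP and HR are the firmest cases. Cytokines qualify if Table 1 is right about the preoperative sample. PaCO2 qualifies only if its baseline proves to be pre-treatment. The primary POD 1 QoR-40 comparison and the sample size are not touched by this point.

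**What to change.** In the Statistical analysis section, state that TNF-α, IL-1β, IL-6, MAP and HR are compared on post-baseline times with the patient's own baseline as covariate, by ANCOVA or a mixed model with group, time and group-by-time. Name the contrast: the adjusted group difference averaged over the post-baseline times, with the difference at each time also reported. State that baseline is not a level of the time factor. Analyse cytokines on the log scale, with log baseline as covariate, if they are skewed. Add PaCO2 once its baseline is confirmed to precede treatment.

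Reconcile the cytokine times under Data collection and registration with Table 1. If no preoperative sample is taken, the covariate does not exist and the cytokine comparison is of post-baseline values alone.

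The cost is a few sentences, about one degree of freedom per model, and the need for a baseline value in each patient analysed. SPSS, which the protocol already names, fits these models. If Table 1 stands, no new measurements or patients are needed.

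### Free improvement: QoR-40 is measured before surgery, but the protocol's listed tests make no use of it in the POD 1 comparison, so available precision is forgone

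*Protocol*

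**What the plan says.** The primary endpoint is one score at one time: "The primary outcome of this study is global Quality of Recovery-40 (QoR-40) score on POD 1" (Protocol, Primary outcomes).

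In Appendix A, Table 1, the QoR-40 row is marked at the preoperative visit and at 24, 48 and 72 hours after surgery. Randomisation is marked two hours before surgery, so the preoperative score is obtained before allocation.

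For group comparisons the Statistical analysis section says: "The differences between groups will be analyzed by independent t-test, repeated measures analysis of variance, or Mann Whitney rank sum test", and the list ends with "Chi-squared test, or Fisher exact test as appropriate". It names no covariate-adjusted method and does not say which test applies to the primary outcome. On baseline data it says: "The demographic data and baseline characteristics will only be expressed using descriptive statistics and will not be compared between groups".

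The Sample size estimation section takes as its target that "the minimal clinically important difference (MCID) of QoR-40 score was 6.3 points", states that "based on our institutional data, the Standard Deviation was 9.3 points", and concludes that "36 patients in each group would be required with a power of 80% and at an α level of 0.05". The significance rule is "A two-sided P value < 0.05 indicates a statistically significant difference".

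**The concern.** Patients differ in QoR-40 before surgery, and part of that difference is likely to persist on POD 1. An unadjusted comparison leaves that part in the error term, although the score that would remove it is already being collected. Any chance difference between the groups in preoperative score also passes into the estimate. The trial expects about 72 evaluable patients and has a target difference of 6.3 points, so the width of the confidence interval matters for the conclusion.

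A smaller point goes with this. For a single POD 1 score, both the t-test and the Mann-Whitney test fit the text, and no criterion for choosing between them is given. Naming one adjusted primary analysis would settle that as well.

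**Working it through.** **Inputs.** Difference 6.3, SD 9.3, power 80%, alpha 0.05, 36 per group, 10% dropout and 80 enrolled come from Sample size estimation. The two-sided test comes from Statistical analysis. The correlation r between preoperative and POD 1 QoR-40 is not in the document; it is assumed, with a range of 0.2 to 0.7.

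**Step 1: the plan's own figure.** For an unadjusted two-sample t-test with n per group:

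- standard error = SD × √(2/n) = 9.3 × √(2/36) = 2.192
- noncentrality = 6.3 / 2.192 = 2.874, with 2n − 2 = 70 degrees of freedom
- exact power = 80.9% at n = 36 and 79.8% at n = 35

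So 36 is the smallest n that reaches 80%. With dropout, 36 / 0.9 = 40 per group, or 80 in total. The stated sample size reproduces as an unadjusted t-test.

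**Step 2: the same comparison with the preoperative score as covariate.** Residual SD = 9.3 × √(1 − r²), with 2n − 3 = 69 degrees of freedom at n = 36. The formula ignores the very small further loss from chance covariate imbalance. For r = 0.5:

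- residual SD = 9.3 × √0.75 = 8.05
- standard error = 8.05 × √(2/36) = 1.90
- noncentrality = 6.3 / 1.90 = 3.32, giving power 90.5%

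| Assumed r | Variance removed (r²) | Residual SD | Power at 36 per group | n per group for 80% | 95% CI half-width at 36 per group |
|---|---|---|---|---|---|
| unadjusted | – | 9.30 | 80.9% | 36 | 4.37 |
| 0.2 | 4% | 9.11 | 82.4% | 34 | 4.28 |
| 0.3 | 9% | 8.87 | 84.4% | 33 | 4.17 |
| 0.5 | 25% | 8.05 | 90.5% | 27 | 3.79 |
| 0.6 | 36% | 7.44 | 94.3% | 23 | 3.50 |
| 0.7 | 49% | 6.64 | 97.8% | 19 | 3.12 |

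The gain in power is 82.4 − 80.9 = 1.5 points at r = 0.2, 3.5 at 0.3, 9.6 at 0.5 and 13.4 at 0.6.

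**Step 3: the open choice between t-test and Mann-Whitney.** In 20,000 simulated null trials per setting (36 per group, normal data), taking the smaller of the two P values gave a type I error of 5.8% to 6.0% against the nominal 5%. In a separate simulation of 10,000 null trials, letting a normality check choose the test gave 5.0%. The excess is therefore about one percentage point, and it arises only if the test is picked after the results are seen.

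**The case against.** Four objections deserve an answer.

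**The unadjusted test is valid.** In a randomised comparison it is unbiased in expectation, chance imbalance is already covered by its 5% error rate, and it matches the sample size calculation. This stands in full.

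**Covariate adjustment often belongs in the SAP, which is not at hand.** This stands in part. The sentence restricting baseline characteristics to description does not forbid adjusting for preoperative QoR-40. Table 1 lists baseline characteristics under enrolment and QoR-40 under outcome assessment, so the text is silent on that score. But the protocol does set out its between-group methods for continuous outcomes, and none of them is adjusted. Improving that list is a fair recommendation on the protocol itself.

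**The gain rests on an unknown correlation.** This stands. At 0.2 to 0.3 the benefit is modest, and the document offers nothing to narrow the range.

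**The choice of test is narrower than the list suggests.** A reader might infer that all three methods for continuous data compete for the primary outcome, so that the error rate is seriously inflated or the power could collapse under repeated-measures ANOVA. The documents do not support this. The primary outcome is a single POD 1 score. Repeated-measures ANOVA belongs naturally with the serial data, such as haemodynamics at five time points and cytokines and pain at 2, 6 and 24 hours. Its power for QoR-40 over POD 1 to 3 also depends on an assumed time course: a constant 6.3-point effect would give 93% or 89% at between-day correlations of 0.5 or 0.7, while an effect that fades would give less. The protocol specifies neither the course nor the correlation.

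**Conclusion.** The point holds as a free improvement. The preoperative score is scheduled before allocation, the listed methods do not use it, and adjusting for it would sharpen the primary comparison at no data cost. At 36 per group, power would rise from 80.9% to between 82.4% and 94.3% for assumed correlations of 0.2 to 0.6, and the 95% confidence interval half-width would fall from 4.37 to between 4.28 and 3.50 points. These figures rest on the protocol's SD of 9.3, a linear relation between the two scores, and a correlation that the document does not give.

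Two stronger conclusions should not be drawn. The trial is not underpowered without adjustment, and the unadjusted t-test is not wrong. Nor does the unnamed primary test carry the point by itself: its cost is a type I error of about 6%, and only if the test is chosen after the results are known.

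**What to change.** In the Statistical analysis section of the protocol, state that the primary analysis is an ANCOVA of POD 1 QoR-40 on treatment group with preoperative QoR-40 as covariate, reporting the adjusted mean difference with its 95% confidence interval so that it can be read against the 6.3-point target. Name the Mann-Whitney test on POD 1 QoR-40 as a sensitivity analysis. This also removes the open choice between t-test and Mann-Whitney.

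Keep the sample size as it is. Since the correlation is unknown, treat the extra precision as a margin and not as a reason to enrol fewer patients. Make the change before anyone sees outcome data by group, including at the interim analysis mentioned under Data collection and registration.

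The cost is a few lines of wording. The preoperative questionnaire is already scheduled, so no patients, visits or measurements are added.
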